### Outcome measures

The primary outcome measure is the woman’s EPDS assessed at 34–36 weeks of gestation and at 4–6 weeks postnatally.

Secondary outcomes are GAD7 scores to assess maternal anxiety levels, IES-R score to assess PTSD and pregnancy complications, including occurrence of mental health disorders, rate of preterm birth, rate of induction of labour, rate of vaginal birth, elective caesarean sections on maternal request as well as other birth outcomes.

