#### Psychological assessments

EPDS^41 42^ is a widely validated screening instrument. A high EPDS score does not in itself confirm a diagnosis of depression. A score above a certain cut-off point may, however, indicate probable depressive disorder. In the present study, the EPDS will be administered in the third trimester of pregnancy (a 34–36 weeks) and at 4–6 weeks postpartum. An EPDS cut-off score of >10 has been found to be optimal for perinatal screening for depression.^43^

*The* GAD7 questionnaire^44 45^ has been translated into Chinese and validated in general hospital outpatients, with a cut-off score of >10^22^ to indicate anxiety.

IES-R will be used to assess PTSD. It has been translated and validated in Chinese^46–48^ to assess symptoms of PTSD corresponding with Diagnostic and Statistical Manual of Mental Disorders (DSM-V).^46 47^ A survey about COVID-19 will also be administered at the same time points (at 34–36 weeks of gestation and 4–6 weeks postpartum).

The EPDS, GAD7 and IES-R scales were chosen over psychodiagnositc interviews because they show high reliability and validity and are more cost-effective and efficient compared with psychodiagnostic interviews.^49^

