### Sample size and power calculation

The sample size was calculated using an online sample size calculator (CinCalc.com) to detect a 20% difference in mean EPDS scores between the intervention versus control groups with a 80% power and an alpha of 0.05 in each study location.^50^ EPDS scores show a normal distribution with a mean of 12.5 and SD of 4.0.^51^ A difference of 20% in the primary outcome is of clinical relevance with regards to the symptomatology of PPD.^52^ Based on this, the calculated sample size is 40 participants in each arm (intervention/control) of the study in each study location (n=80 participants per city). Taking into account and possible dropouts, we estimated a required sample size of 100 participants for each city (study location). The same principle will be applied if any additional study locations are added to this multicentre RCT.

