### Statistical methods

Data will be analysed per protocol using an intention-to treat method. Average EPDS, GAD7 and IES-R scores will be compared between the intervention and control groups and across time points (prenatal and postnatal), using independent sample t-tests. Differences in proportions will be assessed using χ^2^ test. The non-normally distributed continuous variables will be analysed with the Mann-Whitney U test, and the results of the intervention will be analysed by Cohen’s effect size. Multiple imputations will be used for missing data. The variables used in the imputation mode will be previous EPDS score, education level and parity. All patients’ demographic data, retrieved from web survey, will be analysed by descriptive (mean, median and range) statistics. For categorical variables, absolute frequency, percentages and/or proportions will be calculated. χ^2^ or Fisher’s exact test will be used for comparison between groups. For the primary outcome measure, a two-sided p value of <0.05 will be considered significant. Subgroup analyses will be performed for several subgroups of EPDS scores. Spearman’s correlation test will be used to test the correlation between maternal antenatal mental health characteristics assessed by EPDS, GAD7 and IES-R at <34–36 weeks and at 6 weeks postpartum.

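### As written, a missing postnatal GAD7 or IES-R is imputed without the woman's own antenatal score on that scale, which pulls the planned antenatal–postnatal correlations toward zero if they are run on imputed data

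*Protocol article*

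**What the plan says.** The Statistical methods section of the protocol article states "Multiple imputations will be used for missing data", with no restriction to the primary outcome. The next sentence gives the predictors: "The variables used in the imputation mode will be previous EPDS score, education level and parity". No other imputation model appears in the article.

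The same section uses all three scales in its analyses. It plans that "Average EPDS, GAD7 and IES-R scores will be compared between the intervention and control groups and across time points (prenatal and postnatal"), and that "Spearman’s correlation test will be used to test the correlation between maternal antenatal mental health characteristics assessed by EPDS, GAD7 and IES-R", with an antenatal and a postpartum time point named. Under Outcome measures, "Secondary outcomes are GAD7 scores to assess maternal anxiety levels, IES-R score to assess PTSD".

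On timing, Psychological assessments gives the EPDS visits explicitly and adds a COVID-19 survey "at the same time points (at 34–36 weeks of gestation and 4–6 weeks postpartum"). Together with the planned prenatal and postnatal comparison of all three scales, this means that GAD7 and IES-R are also collected at both visits.

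**The concern.** An imputation model should contain the variables that the later analysis relates to one another. The list follows this principle for EPDS, where the previous score on the same scale is a predictor, but not for GAD7 or IES-R. A woman who answers at 34–36 weeks and misses the postnatal survey has her earlier GAD7 and IES-R on file, and the rule does not use them.

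Two consequences follow:

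- **Correlations.** The imputed postnatal value is unrelated to the woman's antenatal value on that scale, given EPDS, education and parity. The imputed pairs therefore carry too little of the correlation that is being estimated. This happens even when data are missing completely at random.
- **Comparisons between arms.** If women with higher antenatal anxiety or stress are more likely to miss the postnatal survey, the variable that would make missing-at-random plausible for those scales is collected but left out of the model.

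**Working it through.** **The plan's own figure.** The Sample size section takes a 20% difference on a mean of 12.5 (2.5 points) with SD 4.0, "with a 80% power and an alpha of 0.05 in each study location". The normal formula gives 2 × (1.960 + 0.842)² × 4.0² / 2.5² = 40.2 per arm, or 41 rounded up, against the stated 40 (power at 40 per arm is 79.8%). The step from 80 to 100 per city implies a 20% dropout allowance, since 80 / 0.80 = 100. This reproduces. The plan gives no figure for the imputation or the correlations.

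**Inputs for the check.** The predictors and the two visits come from the protocol. All correlations below are assumptions, because the article gives none. Education and parity are taken to add little beyond EPDS.

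**Step 1: expected correlation after imputation.** Let m be the share of women with an antenatal score but no postnatal score, missing completely at random. Observed pairs have the true own-scale correlation r_own. Imputed pairs are linked only through antenatal EPDS. The pooled value is about

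(1 − m) × r_own + m × r(antenatal EPDS, antenatal GAD7) × r(antenatal EPDS, postnatal GAD7).

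With r_own 0.60, same-visit 0.60 and cross-visit 0.45, the imputed pairs have correlation 0.60 × 0.45 = 0.27:

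| m | Calculation | Result (true 0.60) |
|---|---|---|
| 10% | 0.9 × 0.60 + 0.1 × 0.27 | 0.567 |
| 20% | 0.8 × 0.60 + 0.2 × 0.27 | 0.534 |
| 30% | 0.7 × 0.60 + 0.3 × 0.27 | 0.501 |

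With r_own 0.50 and the rest unchanged, m = 20% gives 0.8 × 0.50 + 0.2 × 0.27 = 0.454.

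Over r_own 0.5–0.7, same-visit 0.5–0.7 and cross-visit 0.35–0.45, the relative loss is about 4–8% at 10% missing, 7–15% at 20% and 11–23% at 30%.

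**Step 2: simulation of the correlation.** Proper multiple imputation was simulated with 100 women per city, 10 imputations, 500 runs, own-scale 0.60, same-visit 0.60 and cross-visit 0.40. At 20% missing completely at random, Spearman's coefficient was 0.60 in complete data, 0.53 when imputing from EPDS only, and 0.60 with the own antenatal score added. At 10% missing it was 0.56 against 0.60, and at 30% it was 0.49 against 0.59. Adding treatment arm without the own score left it at 0.53 at 20% missing.

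**Step 3: simulation of the arm difference.** The true difference was −0.50 SD and about 20% of postnatal scores were missing. In the rows where missingness depends on antenatal GAD7, its log-odds slope was 1.0 per SD.

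| Missingness | EPDS only, no arm | + own score, no arm | EPDS + arm | + own score + arm |
|---|---|---|---|---|
| Completely at random | −0.45 | −0.47 | −0.51 | −0.51 |
| Depends on antenatal GAD7, alike in both arms | −0.43 | −0.47 | −0.48 | −0.50 |
| Depends on antenatal GAD7, opposite directions by arm (extreme) | −0.31 | −0.46 | −0.35 | −0.51 |

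Under random missingness with arm included, the own score changes only precision (SD of the estimate 0.223 without it, 0.219 with it). About half of the shrinkage in the first column of that row goes when the own score is added and all of it goes when arm is added. The absence of treatment arm from the list is a separate point on the same sentence.

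**The case against.** **The list may be meant for EPDS only.** The previous EPDS score is the own-scale predictor for the primary outcome, and the models for the other scales could sit in a fuller document. This is possible but not written. The sentence on imputation covers missing data without limit and one list follows it. The sentence as it stands needs correcting, although the article nowhere says in terms that GAD7 is imputed from EPDS.

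**The correlation analysis is loosely worded.** The phrase "test the correlation between maternal antenatal mental health characteristics assessed by EPDS, GAD7 and IES-R" could mean each scale with itself over time or the scales with one another, and the text does not say that imputed data will be used. Both objections stand, so the attenuation is conditional on both readings.

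**The test result would hardly change.** This also stands. With 80 women, r = 0.53 gives t ≈ 0.53 × √78 / √(1 − 0.53²) = 5.5, and r = 0.60 gives t ≈ 0.60 × √78 / √(1 − 0.60²) = 6.6. Both are far beyond p < 0.001. The reported size of the correlation is affected, not its significance.

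**Not every missing score has an earlier one.** Enrolment is at 12–18 weeks, and the text shows no scale before 34–36 weeks (figure 1 is not available). Women lost in between have no own earlier score. The 80-to-100 allowance covers all dropout, so 20% is the top of the range it implies for postnatal-only loss. If half the loss is early, the share is about 10%.

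**A reader might infer that the secondary treatment effects are seriously biased.** The document does not support this. A shift in the imputed mean that is common to both arms cancels in the difference. Material bias with arm in the model appeared only in the extreme case of dropout running in opposite directions by arm, and nothing in the document predicts that.

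**Conclusion.** The concern holds in a limited form. The stated predictor list omits each secondary scale's own earlier score, and adding treatment arm does not repair this.

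If the correlations are each scale with itself over time and are run on imputed data, an assumed 0.60 for GAD7 becomes about 0.57, 0.53 and 0.50 at 10%, 20% and 30% postnatal-only missingness, and an assumed 0.50 becomes about 0.45 at 20%. The same mechanism applies to IES-R. The 30% case would need more loss than the plan allows for. All of these figures rest on assumed correlations.

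For the GAD7 and IES-R comparisons between arms, the omission mainly costs a little precision. It biases the difference only if missingness depends on the earlier GAD7 or IES-R: about 0.02 SD in the simulated case alike in both arms with arm included, and more if the dependence differs by arm. The point concerns secondary analyses and does not touch the primary EPDS sample size.

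**What to change.** Replace the sentence listing the imputation predictors with one stating that each scale is imputed by chained equations from both visits of EPDS, GAD7 and IES-R, plus education level and parity. Each scale's score at the other visit is then always in its model. Whether treatment arm is also added is the separate point on this sentence and can be settled in the same edit. It would help to state at the same time whether the Spearman correlations are each scale with itself over time, and whether they use imputed or observed data.

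The cost is one sentence and a few lines of code. No new data are needed and the sample size does not change.

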**Methods and analysis:**

We plan to conduct a multicentre prospective randomised controlled trial, Mental health of Urban Mothers trial. Pregnant women living in large metropolitan cities will be recruited using internet-based application through non-profit organisations’ websites. The women who consent will be randomised to receive a web-based peer-to-peer support intervention or usual care. Data will be analysed to identify the effects of intervention on Edinburgh Postnatal Depression Score and Generalised Anxiety Disorder 7 scores as well as pregnancy outcomes. The impact of COVID-19 pandemic on maternal stress will be assesed using Impact Event Scale-R. Any differences in outcomes between cities will be addressed in subgroup analyses.

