The study’s assessment of women’s mental health status at the end of the pregnancy provides information on the expected benefits of psychosocial support during antenatal care, with emphasis on cost-effective web-based psychosocial peer-to-peer support as an important alternative care model. Two recent studies have shown that as many as three out of four pregnant women use a pregnancy-related internet application and find these applications beneficial and trustworthy.^65 66^ This is likely to be even more relevant in urban dwellers.

The routines in perinatal mental health screening policies share similarities, yet they are still different in some aspects in Hong Kong and Shanghai. In Shanghai, first universal prenatal health screening policies have been put in place recently, that is, at Shanghai Jiading District Maternity and Child Health Care Hospital and Obstetrics and Gynecology Hospital of Fudan University.^67 68^ Currently, Shanghai provides only limited universal screening for perinatal mental health problems and lacks universal screening on provincial level. Adequate care for all pregnant women with increased risk for developing perinatal mental health problems is currently not available in Shanghai. In Hong Kong, however, universal PPD screening is one of the components of the Comprehensive Child Development Service in maternal and child health clinics, in collaboration with the Hospital Authority and Social Welfare Department.^69^ Further, Hong Kong women attending perinatal healthcare can get access to a webpage provided by the government, promoting the spread of public health information as well as raised awarness about perinatal depression and services provided for pregnant and postpartum women and their families.^69^ The resource allocation for universal screening and access to information might be crucial in order to reduce the burden of disease caused by perinatal mental health disorders on the family and the society. Our study compares the impact of intervention in two different healthcare settings.

As for most randomised trials, the external validity/generalisability of our findings could be limited since we will only target urban-dwelling population who are comfortable in using internet-based applications.

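### The stated imputation variables leave out city and study arm, so pooled imputation would draw the city score levels together and shrink each city's treatment effect toward zero

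*Protocol article*

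**What the plan says.** In the protocol article, Statistical methods, the missing-data approach is "Multiple imputations will be used for missing data", followed by the list: "The variables used in the imputation mode will be previous EPDS score, education level and parity". The section does not say whether imputation is run on both cities together or within each city, and it does not mention study arm.

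The Sample size section makes the city the unit of sizing: the calculation is "with a 80% power and an alpha of 0.05 in each study location", "to detect a 20% difference in mean EPDS scores between the intervention versus control groups", and the same principle is extended to any added location. The abstract (Methods and analysis) states: "Any differences in outcomes between cities will be addressed in subgroup analyses". The Discussion, after describing how screening and access differ between Hong Kong and Shanghai, states: "Our study compares the impact of intervention in two different healthcare settings".

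**The concern.** An imputation model should contain at least the variables that structure the analyses run on the completed data. Here those are study arm, which defines every primary and secondary comparison, and city, which defines the sizing and the promised subgroup comparison. A variable left out of the model is treated as unrelated to the missing score, given the variables that are in it. Imputed values then dilute the differences that the trial sets out to estimate.

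Two results are at stake. One is the treatment effect within each city, for which each city was powered. The other is the contrast between cities, in score level and in treatment effect.

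**Working it through.** **Inputs from the article.** Mean 12.5 and SD 4.0 ("EPDS scores show a normal distribution with a mean of 12.5 and SD of 4.0"); effect 20% × 12.5 = 2.5 points; 80% power, two-sided 0.05; 40 per arm and 80 per city, raised to 100 per city. The implied missing fraction is 1 − 80/100 = 20%.

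**The plan's own figure.** n per arm = 2 × [4.0 × (1.960 + 0.842) / 2.5]² = 40.2. This reproduces the stated 40 to rounding; power at 40 per arm is 79.8%.

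**Assumptions, none given in the article.** True effects of −2.5 in city A and 0 in city B; control-arm city gap g = 2.5; missingness at random within cells; imputation pooled over cities and arms. Education and parity are taken to predict nothing about arm or city. An earlier EPDS is either absent or correlated 0.5 with the missing score. Both cases matter. The Psychological assessments section schedules the EPDS only at 34–36 weeks and 4–6 weeks postnatally, so the text shows no earlier score for the first assessment (figure 1 is not shown). The postnatal assessment does have one.

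**Step 1: the list as written, no earlier EPDS.** Imputed scores have the same expected value in all four cells, so every difference is multiplied by (1 − m), where m is the missing fraction.
- City A effect: 0.8 × (−2.5) = −2.0.
- City B effect: 0.8 × 0 = 0.
- City-by-arm contrast: 0.8 × 2.5 = 2.0 instead of 2.5.
- Control-arm city gap: 0.8 × 2.5 = 2.0.

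With an earlier EPDS at r = 0.5 that shows the same cell differences, a large simulation gives effects of about −2.3 and 0.0, and a contrast and city gap of about 2.3.

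**Step 2: partial and full repairs, no earlier EPDS.**

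| Imputation model | City A | City B | Contrast |
|---|---|---|---|
| As listed | −2.0 | 0.0 | 2.0 |
| Plus city only | −2.0 | 0.0 | 2.0 |
| Plus arm only | −2.25 | −0.25 | 2.0 |
| Plus arm and city, no interaction | −2.25 | −0.25 | 2.0 |
| Plus arm, city, arm-by-city | −2.5 | 0.0 | 2.5 |

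For the arm-only row, the imputed arm effect is the average (−2.5 + 0)/2 = −1.25. City A becomes 0.8 × (−2.5) + 0.2 × (−1.25) = −2.25, and city B becomes 0.2 × (−1.25) = −0.25. With an earlier EPDS at r = 0.5 these are about −2.4 and −0.1.

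**Step 3: unequal dropout.** Assume 30% missing in the intervention arm, 10% in control, and the same true effect of −2.5 in both cities. With city left out, the city gap shrinks to 0.7g in one arm and 0.9g in the other. The two city effects then differ spuriously by (0.9 − 0.7) × 2.5 = 0.5 points. This holds with or without arm in the model. With an earlier EPDS at r = 0.5 the difference is about 0.2 to 0.25.

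**Step 4: at the planned size.** A simulation used 50 per arm per city, 20 imputations and Rubin's rules. It assumed 20% missing in each arm, a true reduction of 2.5 in both cities, a city gap of 2 and one covariate correlated 0.3.

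| Imputation model | Reduction within a city | Power | City gap |
|---|---|---|---|
| As listed | 2.03 | 62% | 1.56 |
| Plus city only | 2.03 | 63% | 2.00 |
| Plus arm only | 2.50 | 81% | 1.61 |
| Plus arm, city, arm-by-city | 2.50 | 79% | 1.98 |

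**The case against.** **Pooling is presumed.** The article does not say that imputation is pooled, and imputing by city with the same variables is compatible with its text. This stands, so the finding on city levels is conditional. It does not rescue the treatment effect: imputing by city without arm still turns −2.5 into about −2.0.

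**A condensed article leaves detail to the analysis plan.** That would answer a missing list. Here the article names the variables, and following that list gives worse results.

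**City analysis is secondary.** The article sizes by city, but names analysis by city only as subgroup analyses in the abstract. The Discussion sentence defines no estimand, and no separate primary test per city is described. This stands and limits the weight of the city contrast. A reader might infer that each city has its own primary analysis; the article does not say so.

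**A reader might infer that one city's treatment effect leaks into the other and creates a false effect where there is none.** Under the written list it does not. With arm absent, imputed scores carry almost no arm difference to pass on, and the null city stays near 0. Leakage appears only if arm is added without city-by-arm.

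**The biases are small against sampling error.** With 40 per arm, the standard error is 4 × √(2/40) = 0.89 for a city effect and 4 × √(4/40) = 1.26 for the contrast. The leakage of 0.1 to 0.25 points is well below either. The loss from omitting arm, about 0.5 points and some 17 percentage points of power, is not trivial.

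**With equal dropout and a common effect, leaving out city alone does no harm within a city.** This is correct once arm is in the model (2.50 in the table). Bias then needs effects or dropout that differ, and the article gives no evidence of either.

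**Conclusion.** The concern holds in a limited form. The stated imputation list omits both city and study arm, although each city is powered separately and a city comparison is promised. If pooled imputation follows the list, city levels are drawn together and each city's effect shrinks toward zero. At 20% missing the loss is about 20% without an earlier EPDS (2.5 to about 2.0) and about 8% with one at r = 0.5 (2.5 to about 2.3). Unequal dropout of 30% against 10% would add a spurious city difference of up to about 0.5 points.

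The omitted arm is the larger fault. City matters for the level comparison, for unequal dropout, and because adding arm without city-by-arm would begin to mix the two cities' effects. The sizes rest on the assumed effects, city gap, correlation and pooling; only the 20% is implied by the article's own dropout allowance.

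**What to change.** Amend the sentence on imputation variables in Statistical methods. Either impute separately within each city-by-arm cell, or add study arm, city and arm-by-city to the variables already listed. State that this applies to every study location, including any added later. Imputing by city without arm, or adding arm without the interaction, is not enough.

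The cost is one sentence. The small downside is slightly noisier imputation models with about 100 women per city: in the planned-size simulation, power was 79% with the full model against 81% with arm only, when both cities truly had the same effect.
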